## Abstract

**Background:**

Treatment of end stage renal disease has an impact on patients’ physical and psychological health, including quality of life (QoL). Nowadays, it is known that reducing the dialysis period has many advantages regarding QoL and medical outcomes. Although preemptive transplantation is the preferred strategy to prevent patients undergoing dialysis, its psychological impact is unknown. Moreover, transplantation can be experienced in a completely different manner among patients who were on dialysis and those who still had a functioning kidney at the time of surgery. Longitudinal data are often collected to allow analyzing the evolution of patients’ QoL over time using questionnaires. Such data are often difficult to interpret due to the patients’ changing standards, values, or conceptualization of what the questionnaire is intended to measure (e.g. QoL). This phenomenon is referred to as response shift and is often linked to the way the patients might adapt or cope with their disease experience. Whether response shift is experienced in a different way among patients who were on dialysis and those who still had a functioning kidney at time of surgery is unknown and will be studied in the PreKit-QoL study (trial registration number: NCT02154815). Understanding the psychological impact of pre-emptive transplantation is an important issue since it can be associated with long-term patient and graft survival.

**Methods/Design:**

Adult patients with a pre-emptive transplantation (n = 130) will be prospectively included along with a control group of patients with a pre-transplant dialysis period < 36 months (n = 260). Only first and single kidney transplantation will be considered. Endpoints include: comparison of change between groups in QoL, anxiety and depressive disorders, perceived stress, taking into account response shift. These criteria will be evaluated every 6 months prior to surgery, at hospital discharge, at three and six months, one and two years after transplantation.

**Discussion:**

The PreKit-QoL study assesses and compares the evolution of QoL and other psychological criteria in preemptive and dialyzed patients taking patients’ adaptation into account through response shift analyses. Our study might help to conceive specific, adapted educational programs and psychological support to prevent a possible premature loss of the kidney as a consequence of non-compliance in patients that may be insufficiently prepared for transplantation.

**Trial registration:**

ClinicalTrials.gov identifier NCT02154815, registered on May 28, 2014

## Background

### End stage renal disease, dialysis and transplantation

Chronic kidney disease can lead to end stage renal disease (ESRD), which requires use of substitution techniques such as hemodialysis, peritoneal dialysis or kidney transplantation. Treatment of ESRD is cumbersome in terms of implementation, impact on the physical and psychological health of patients, quality of life (QoL) and it generates substantial health expenditures. It is well-known that kidney transplantation in eligible ESRD patients is the treatment of choice compared to long-term dialysis [1] since it is associated with longer survival [2]. Furthermore, the cost of transplantation is lower as compared to dialysis. Some studies have also described higher QoL for kidney transplant recipients compared to patients undergoing dialysis [3, 4] as well as more positive perceptions of illness when changing from dialysis to transplantation [5]. Hence, limiting the dialysis period before transplantation has several advantages in terms of medical outcomes, QoL and costs. In respect with the same arguments, one can expect that preemptive transplantation, i.e. the patient is placed on the transplant waiting list and transplanted prior to progression to ESRD, would be the preferred strategy. Nevertheless, the literature does not provide a clear answer regarding the benefit of preemptive transplant and even less is known about its psychological impact and its possible burden for patients: for instance, patients may not be aware of the benefit of transplantation compared to dialysis but in contrast may suffer from the consequences of transplantation. Although it is recommended to enlighten patients of all possible consequences and complications after the transplantation, patients are sometimes anyway startled since for instance they suffer after the surgery, or are uncomfortable with the load of the immunosuppressive therapy. Furthermore, in transplantation centers, it has been observed that patients receiving a preemptive transplant may consider or perceive transplantation as an event that has deteriorated their well-being [6].That may explain the high variability of preemptive transplant practice worldwide [7]. This lack of data regarding the psychological impact of preemptive transplantation constitutes a true issue since these subjective outcomes can be associated with the long-term patient and graft survival [8]. This issue is important regarding the collective impact of early registration on waiting list: preemptive transplantations are associated with an increase in the duration on waiting lists, which remains an important risk factor of graft failure. In fact, no data allows concluding on post-transplant QoL in particular because transplantation can be experienced in a completely different manner among patients who were on dialysis and those who still had a functioning kidney at the time of surgery.

### Psychological impact of dialysis and transplantation

Studies assessing the psychological impact and QoL of Patients with Preemptive Transplantation (PPT) compared with Patients with Dialysis before Transplantation (PDT) are lacking and it cannot be assumed that preemptive transplantations systematically improve patients’ QoL. Indeed, if few disease limitations and symptoms were experienced before transplantation, the aftermath of the graft may seem disproportionate, especially in case of post transplantation complications (infection, acute rejection, etc.). Moreover, these patients in ESRD who are not on dialysis have to simultaneously be psychologically prepared for dialysis and transplantation, without knowing which of the two treatments they will have to face first. Some patients may prepare for dialysis and then be referred for a transplant instead, for which they are not ready. In contrast, other patients might await transplantation and perceive dialysis as a failure. In this setting, a better understanding of how patients anticipate, live and face pre and post-transplantation and its consequences can contribute to enhance and better orientate educational programs to improve patient care.

### Longitudinal data and response shift

The importance of studying longitudinal evolution of perceived QoL of patients with chronic disease and in identifying its possible associated factors is now well admitted [9–11]. Such QoL data are often collected through questionnaires including different items called Patient-Reported Outcomes (PRO). Despite the fact that PRO are nowadays considered simple, valid and reliable measures of QoL, it is however clear that the cognitive processes involved in completing them are quite complex [12] and that longitudinal PRO data might sometimes be very difficult to interpret. Indeed, some studies have evidenced a stable or even a higher level of perceived Qol in patients with severe chronic conditions, despite a poor physical health state, as compared to the general population [13–15]. By contrast, others have shown opposite results for stable patients, regarding their health status across occasions, reporting changes in QoL. This phenomenon, which might be regarded as a paradox, is sometimes referred to as response shift (RS) [16, 17]. In case of RS, there is a change in the meaning of what the PRO (QoL, anxiety, pain, etc.) is intended to measure over time or in the patient’s expectations and life priorities according to the disease evolution. It is often linked to the way the patients might adapt or cope with their disease experience. RS can result from three different processes [16, 17]: 1) changes in the patient’s internal standards of measurements called recalibration (i.e. the level of QoL or anxiety measured by the questionnaire can be interpreted differently before and after transplantation), 2) changes in the patient’s values and in the relative importance given to the questions or dimensions of QoL that are appraised before and after transplantation, called reprioritization, and 3) changes in the patient’s definition of what is being measured over time called reconceptualization. Hence, it might be problematic or even impossible to distinguish, without appropriate methods, true QoL changes from confounding RS effects. Indeed, patients may give different answers to the PRO over time, not only because their health has changed, but also because their perception on what health or QoL means to them has changed. The accurate assessment of the effect of transplantation for instance can then be obfuscated by RS and lead to biased results, poor power to detect effects of interest and therefore, erroneous conclusions [18–21]. Indeed, RS can seriously alter the psychometric properties of PRO such as reliability, validity and ability to detect true changes (responsiveness) [22]. On the other hand, one can also highlight the therapeutic importance that the phenomenon of RS constitutes in itself by allowing a better understanding of how patients adjust to their illness. RS may well also be one of the goals of therapy in helping patients to cope with their illness and to live with it. Therefore, RS can be viewed either as a nuisance (measurement bias) or as an indication of a possible therapeutic benefit coming from some form of psychological adaptation or adjustment. In fact, it is very likely that the post-transplant QoL experienced by patients for whom first replacement therapy was transplantation might be lower than for patients who have undergone dialysis, even for a short period of time [1, 23]. The rigorous comparison of change in the QoL of preemptive kidney transplant patients and patients who were on dialysis requires taking into account the very likely occurrence of the RS phenomenon, not only in terms of detection, but also in terms of statistical adjustment in the analysis of changes in PRO data.

### Aims and objectives

Our hypothesis is that preemptive kidney transplant recipients have a lower quality of life and present more difficulties regarding psychological adaptation after transplantation compared to patients who were under dialysis before surgery for less than 3 years. The designed project aims at providing a better assessment and understanding of the psychological impacts and of patients’ psychological adaptation, taking into consideration the response shift, as well as patient and graft outcomes following preemptive transplantation. This could help optimizing the management of these patients, particularly regarding therapeutic education programs and adapted implementation of psychological support.

## Methods/Design

### Study design

The PreKit-QoL study is a prospective, multicenter, controlled study of quality of life, psychological adjustment process and medical outcomes of patients receiving a preemptive kidney transplant (PPT group) compared to a similar population of recipients after a dialysis period of less than three years (PDT group). The clinical and psychological data as well as the QoL questionnaires will be prospectively collected in the PPT and the PDT groups. Both groups will be matched regarding the recipient gender and the transplantation centers which are the two parameters differentially distributed between the two groups in our prospective cohort DIVAT (www.divat.fr). The type of donors (deceased or living) will be also matched between PDT and PPT. Since it is important to assess QoL before transplantation in order to evaluate response shift related to transplantation, the questionnaires will be collected for all patients waiting a first transplantation without dialysis or with a dialysis period of less than 36 months. Data will be collected at transplantation (sex, age, immunization, medical history, etc.). Other data that change over time, such as QoL, will also be collected every six months before transplantation, at hospital discharge, and 3, 6, 12 and 24 months after transplantation. The flowchart of the study is presented in Fig. 1.

**Fig. 1 Fig1:**
[figure not shown]
Flowchart of the PreKiT-QoL study. Mx: x months after transplantation, x = 3, 6, 12, and 24

### Study setting and participants

Patients will be mainly recruited from the University Hospital centers participating in the DIVAT network (*Données Informatisées et VAlidées en Transplantation*, 6 centers in France: Nantes, Paris Necker, Paris Saint-Louis, Nice, Lyon). The University Hospitals of Marseille and Toulouse will also participate in the study. The duration of inclusion will be four years. Data collection will take place over six years including the 2-year follow-up of the last included patient. In total, the study will take place over a period of seven years to allow for data analysis. It is a non-interventional research study (routine care), all investigators have agreed to provide patients with clear and precise information about the protocol and will give a copy of the information form to the patients. The patient will be enrolled in the study after reading the information form and signing and dating it. Both documents will be issued in duplicate hard copy format so that the patient and the investigator can each keep a copy. The investigator’s original will be placed in the investigator’s file.

### Inclusion criteria

All patients will be over 18 years old without being under guardianship. All patients with a preemptive transplantation from deceased or living donors will be prospectively included in the PreKit-Qol study. Only first kidney transplantations without other transplanted organ will be considered.

### Primary outcome measure

The primary outcome will be the change in QoL, taking into account the possible occurrence of response shift. This criterion will be measured by a specific questionnaire ReTransQol developed for kidney transplant recipients [24]. It will be evaluated every 6 months prior to surgery, at hospital discharge, and three months, six months, one year and two years after the transplantation.

#### Secondary outcome measures

The following outcomes will be compared between PPT versus PDT:The change in generic QoL, subjective well-being, perceived anxiety and depressive disorders as well as perceived stress during follow-up (every 6 months before the surgery, at hospital discharge, 3, 6, 12, and 24 months post-transplantation) taking into account the possible occurrence of response shift. Generic QoL will be assessed with the SF-36 questionnaire. This questionnaire has the disadvantage of not being specific, and therefore less sensitive to specific changes in the health status of the recipient. However, it allows a comparison of the results to a reference population [25] and allows an easier comparison of the patients in different therapeutic frameworks (for example patients before and after transplantation). Subjective well-being, anxiety and depressive disorders, and perceived stress will be assessed using the satisfaction with life scale (SWLS) [26, 27], the Hospital Anxiety and Depression scale (HAD) [28, 29], and the Perceived Stress Scale (PSS) [30], respectively.Coping strategies (process of managing stressful circumstances) and post-traumatic growth (positive psychological change experienced as a result of the struggle with highly challenging life circumstances) at 6 and 24 months post-transplantation. Coping strategies and post-traumatic growth will be assessed using with the Brief Cope [31] and the Posttraumatic Growth Inventory (PTGI) [32], respectively.The post-transplantation graft and patient outcomes collected at hospital discharge, and 3, 6, 12 and 24-months post-transplantation: i) evolution of the Graft Filtration Rate (GFR) that will be estimated using the 4-variables MDRD formula [33], ii) evolution of the daily proteinuria that will be diagnosed by a simple dipstick test.The Kidney Transplant Failure Score at one year post-transplantation [34]. The KTFS is able to predict death-censored graft survival.The post-transplantation time to return to work, if appropriate.The compliance of patients will be assessed every six months prior to surgery, at hospital discharge, and at 3, 6, 12, and 24 months with the Girerd questionnaire [35].

In addition, other collected clinical data as well as variables related to the social status of the recipient are given in Table 1. The schedule of the study is presented in Table 2.

**Table 1 Tab1:** Clinical variables directly extracted from the DIVAT data bank

Recipient	Age, gender, weight, height, clinical center, initial disease (glomerulonephritis, diabetes, etc.), cold ischemia time, HLA A-B-DR incompatibilities, number of post transplantation dialyses, pre-transplantation anti HLA immunization whatever the technique used within the six months prior to surgery, cardiovascular history, cancer history, hypertension history, diabetes history, pre transplantation dialysis technique, previous educational program.
Donor	Age, gender, last serum creatinine level, cause of death, hypertension history.
Dates	Birth, first dialysis, registration on waiting list, transplantation, acute rejection episodes, return to work, return in dialysis, last follow-up, death.
The biological follow-up at hospital discharge, three, six, 12 and 24 months	The creatininemia (1) and the daily proteinuria.

(1). The creatininemia will also be collected before the surgery in order to adjust our analysis on the renal function: the psychological impact of the transplantation may depend on the previous grade of renal insufficiency

**Table 2 Tab2:** Schedule of the PreKiT-QoL study

Activities	Every six months before transplantation	Hospital discharge	M3	M6	M12	M24
Demographic data		X				
Previous medical history		X				
Transplantation data		X				
Donor data		X				
Creatininemia and proteinuria		X	X	X	X	X
ReTransQol questionnaire	X	X	X	X	X	X
SF36 questionnaire	X	X	X	X	X	X
Satisfaction with Life Scale (SWLS) questionnaire	X	X	X	X	X	X
The Perceived Stress Scale (PSS)	X	X	X	X	X	X
The Brief Cope				X		X
The Hospital Anxiety and Depressions Scale (HAD)	X	X	X	X	X	X
The Post-Traumatic Growth Inventory (PTGI)				X		X
Compliance questionnaire	X	X	X	X	X	X
Kidney Transplant Failure Score (KTFS)					X	

X: collected data. Mx: x months after transplantation, x = 3, 6, 12, and 24X: collected data. Mx: x months after transplantation, x = 3, 6, 12, and 24

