### Sample size

Computation of a minimum required sample size is not statistically feasible for this study based on the observation of perceived QoL and psychological data taking into account the possible occurrence of RS. Indeed, the concept of RS is complex and novel in this disease and we have no preliminary data or any clear expectation for the results. The sample size will therefore be driven by the inclusion capacities of each center involved in the PreKiT-QoL study. Based on the extraction of the DIVAT data bank of the recipients transplanted between 2010 and 2012, one can expect that at least 130 recipients with preemptive transplantation (case) can be included during the four years inclusion period of the protocol. For each case, two control recipients who have experienced a pre-transplant dialysis period of less than 36 months will be included matched on gender, transplant center, and type of donor. A total of 390 patients will be included. This ratio 1:2 has been chosen to increase the sample size and the statistical power, the main expected limitation being the inclusion of patients receiving preemptive transplantation.

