Change in coping strategies and in post-traumatic growth will be measured at 6 and 24 months after transplantation and assessed using linear mixed models [40]. The GFR will be measured at hospital discharge, and 3, 6, 12, and 24 months post-transplantation and estimated using the MDRD formula [33]. A linear mixed model will also be used to handle these longitudinal measurements. Three explicative variables will be systematically taken into account: post-transplantation time, preemptive transplantation (yes/no) and the interaction between them. According to the non-linear relationship between the post-transplantation time and the GFR evolution [41], two slopes will be modeled with a breakpoint at 6 months. For all linear mixed models, random terms will be included on the intercept, on the slopes or both. Univariate (p < 0.2) and multivariate (p < 0.05) analyses will be performed in order to take into account possible confounding factors. The daily proteinuria will be measured at hospital discharge, and 3, 6, 12 and 24 months post-transplantation. This random variable is not Gaussian. A Gamma distribution is more appropriate but since a generalized linear models with such an inverse function as canonical link function will be difficult to interpret, the proteinuria will be divided into two classes for analysis: ≤0.5 g/24 h or >0.5 g/24 h. A logistic model with random effects will therefore be used [40]. The KTFS is a score that is computed at one year. The mean score at one year will be compared using a Student’s t-tests for paired data between the PPT and PDT groups.

The statistical significance level will be set at 5 % (type I error).

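### Proteinuria is said to be read by dipstick but is modelled as a daily quantity cut at 0.5 g/24 h, and the reason given for the cut is avoidable

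*Protocol article*

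**What the plan says.** Three places in the protocol article describe this outcome.

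- **Secondary outcome measures** lists, among the graft outcomes at discharge and at 3, 6, 12 and 24 months, the "evolution of the daily proteinuria that will be diagnosed by a simple dipstick test".
- **Table 1**, headed as clinical variables extracted from the DIVAT data bank, lists for the biological follow-up: "The creatininemia (1) and the daily proteinuria". It gives neither method nor unit. Table 2 repeats the visits and adds neither.
- **Statistical analysis** says that the variable is not Gaussian, that a Gamma distribution would suit it better, and that "since a generalized linear models with such an inverse function as canonical link function will be difficult to interpret, the proteinuria will be divided". The split is then defined: "the proteinuria will be divided into two classes for analysis: ≤0.5 g/24 h or >0.5 g/24 h". The model follows: "A logistic model with random effects will therefore be used".

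The article gives no clinical reason for 0.5 g/24 h. It mentions no 24-hour collection, no protein/creatinine ratio and no rule for turning a dipstick grade into grams per day.

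**The concern.** There are two separate problems, and they apply under different circumstances.

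**Measurement.** A dipstick returns an ordered grade of concentration in a spot sample. It is not a mass excreted over 24 hours and not a continuous positive variable. A Gamma distribution does not describe it, and a g/24 h threshold cannot be applied to it without a conversion rule. The two statements therefore do not fit together. In a multicentre study, centres that resolve the conflict differently would produce a binary outcome that means different things at different sites. Matching on centre does not define the outcome.

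**Analysis.** If the values are in fact quantitative, the plan discards the continuous measurement because of the link function alone. The canonical link is a convenience and is not required, so the reason given does not lead to dichotomising. What is lost is precision on a graft outcome. The Sample size section names recruitment of preemptive recipients as the main limitation and says that the 1:2 ratio was chosen to raise power.

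**Working it through.** **The plan's own figure.** The Sample size section expects "at least 130 recipients with preemptive transplantation (case) can be included", with two controls per case: 130 + 2 × 130 = 390, as stated. No power, effect size or event rate is given for proteinuria, so there is no proteinuria figure to reproduce.

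**The passages side by side.** Dipstick implies an ordered grade with no daily unit. Gamma implies a continuous positive value. A cut at 0.5 g/24 h needs a daily mass. The second and third are compatible with each other, and the first is compatible with neither. Table 1 says daily proteinuria, which leans towards a quantity but does not settle the method or unit.

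**The link function.** For a Gamma model the inverse link is canonical. With a log link, log(mean) = a + b × group, so exp(b) is the ratio of mean proteinuria between groups.

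**Information kept after the cut (quantitative case only).** The shape k and the proportion p above the cut are assumptions. The calculation takes one visit and ignores matching.

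- Information per patient on the log mean from the Gamma model: k.
- Information from the split: (t·f(t))² / (p(1−p)), where f is the Gamma density with shape k and unit scale, and t is the point exceeded with probability p.
- Fraction kept: (t·f(t))² / (k·p(1−p)).

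For k = 1, t = −ln p and f(t) = p, so the fraction is p(ln p)²/(1−p). At p = 0.2 this is 0.2 × 2.590/0.8 = 0.65.

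| Proportion above cut | k = 0.8 | k = 1 | k = 2 |
|---|---|---|---|
| 50% | 0.45 | 0.48 | 0.55 |
| 20% | 0.65 | 0.65 | 0.63 |
| 10% | 0.61 | 0.59 | 0.53 |

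At 20% above the cut, 130/260 patients behave like about 82-84/164-168 (0.63 × 130 = 82; 0.648 × 130 = 84; doubled for controls).

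**The same in power terms.** Assumed: ratio of means 1.35, control mean 0.2 to 0.5 g/24 h, 130 v 260. The plan states "The statistical significance level will be set at 5 % (type I error") without sidedness, so two-sided is assumed. For the Gamma log-link model, SE = √((1/130 + 1/260)/k). With k = 1, SE = 0.107, ln 1.35 = 0.300, and power = Φ(0.300/0.107 − 1.96) = 0.80.

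| Shape | Gamma, log link | Split at 0.5 g/24 h |
|---|---|---|
| 0.8 | 0.71 | 0.45-0.53 |
| 1 | 0.80 | 0.54-0.62 |
| 2 | 0.98 | 0.78-0.88 |

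The loss is about 9 to 26 percentage points. A simulation of 1,000 runs (shape 1, control mean 0.3 g/24 h) agreed. The log-link model had power 0.79, type I error 0.050 and a back-transformed estimate of 1.35. The split had power 0.63 and type I error 0.058.

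**The case against.** The strongest defence is that a pre-specified threshold with a random-effects logistic model is a valid analysis, and that most of the article (unit, cut, Gamma remark, the word daily in Table 1) points to a quantity, which would make the dipstick phrase one stray clause. The first part stands: the planned test is valid, and the loss is one of efficiency. A clinical case for the cut could also be made, although the article makes none. The second part may well be true, but the documents do not show it.

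Four stronger readings are tempting and are not supported.

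- *The link problem is imaginary.* It is not. The inverse link is canonical for the Gamma and is awkward to interpret. Only the step from there to dichotomising fails.
- *The outcome is both unclassifiable and stripped of information.* These harms rest on opposite premises. With dipstick grades only, there is no continuous value to lose. With quantitative values, patients can be classified.
- *The cut keeps 64%, 49% or 34% of the information at 50%, 20% or 10% above it.* Those figures come from φ(z)²/(p(1−p)), which is for a normal shift on the log scale. The plan names a Gamma distribution, for which the pattern differs: at the shapes used here the loss is smallest at 20% and does not grow steadily as fewer patients exceed the cut.
- *The dipstick wording can simply be deleted because Table 1 supplies the daily value.* Table 1 gives no method or unit, and the Study setting section names two hospitals separately from the DIVAT network. A quantitative value at every centre is not established.

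**Conclusion.** The point holds in two parts. First, the article contradicts itself on how proteinuria is measured, and as written the outcome cannot be classified at 0.5 g/24 h from a dipstick. Confidence in this is high, because it rests on the text alone. Second, the stated reason for dichotomising is insufficient, because the difficulty is avoided by choosing another link.

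The size of the second part applies only if values are quantitative. The split then keeps roughly 45% to 65% of the information over the range examined. That range rests on assumed shapes and prevalences, a single visit and no allowance for matching or for the five repeated measurements, so it shows the order of the loss and does not predict it.

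This is one of several secondary outcomes. The primary quality-of-life and response-shift analysis is not touched. The change should be made, but it does not threaten the study.

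**What to change.** 1. Reconcile Secondary outcome measures, Table 1 and Statistical analysis on what is measured, by which method and in what unit. Confirm it for every centre, including the two named separately from the DIVAT network.
2. **If values are quantitative:** make the main analysis a mixed Gamma model with log link, or a linear mixed model on log proteinuria, with time, group and time × group. Keep the proportion above 0.5 g/24 h as a secondary description. State a convention for undetectable values and a sensitivity check on it, since a constant substituted before taking logs can influence the result if many values are undetectable.
3. **If only dipstick grades exist:** use an ordinal mixed model on the grades, and drop both the g/24 h cut and the Gamma rationale.

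The cost is a query to the centres, revised wording and, in the quantitative case, the convention for undetectable values. Neither branch needs extra patients or visits. If centres turn out to use different methods, more than wording will be needed, and the sponsor should find this out before the analysis is fixed.
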